### Interventions

For the emergency event of COVID-19, standard therapy has been developed in strict accordance with the National Diagnostic and Treatment Protocol (the 7th trial version). For patients, standard therapy is necessary to prevent death and other adverse consequences. On the basis of the guideline therapy, the test group will require a standardized TCMR program consisting of acupressure therapy and Liu Zi Jue Qigong exercises. The program will be performed twice a day at 10 am and 4 pm. Each time, acupressure will be performed first, and then Liu Zi Jue Qigong exercises will continue. Each treatment will last 20 min; thus, a total of 40 min will be needed. The TCMR program will be ongoing during the patient’s stay until the patient is discharged. There will be consensus in advance regarding the acupuncture points, pressure levels, and duration. Liu Zi Jue Qigong exercises will be demonstrated live by the therapists on the first day until the patient is able to perform the exercises skillfully. Patients will be provided with paper and video versions of the exercises to facilitate subsequent practice. Therapists performing rehabilitation therapy will be required to have 10 years of clinical experience in acupressure and Qigong therapy and have undergone rigorous clinical trial training before conducting trials until passing an exam to perform the intervention. Furthermore, both groups of the participants will be allowed to participate in normal exercise under the intervention conditions.

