### Inclusion criteria

Patients will only be recruited if they meet each of the following conditions: (1) meet the critical diagnosis criteria for severe COVID-19 [6], (2) are aged between 20 and 80 years and are male or female, (3) have a stable condition and are conscious and cooperative in the examination, (4) volunteer to join the trial and sign the informed consent form, and (5) promise not to perform other exercise programs.

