### Exclusion criteria

Those who meet one of the following conditions will be removed: (1) patients with complications of other serious underlying diseases, such as chronic obstructive pulmonary disease, obstructive pulmonary disease, coronary heart disease, and hypertension; (2) patients with serious mental illness; (3) patients with cognitive dysfunction who are unable to understand the trial process and rehabilitation content; (4) patients with severe bone and joint diseases (such as spinal arthritis, severe osteoporosis, and periarthritis) affecting limb function and movement; (4) patients with respiratory failure who require mechanical ventilation or patients with shock or combined organ failure requiring intensive care unit (ICU) monitoring and treatment; (5) pregnant or lactating women; and (6) patients who participate in other forms of exercise during the trial.

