### Dropout and suspension criteria

During the intervention period, patients will have the right to withdraw for whatever reason and at whatever time under the protection of the Declaration of Helsinki [16]. In addition, if the hospitalization time is less than 7 days, the subject will be excluded as the outcome evaluation cannot be completed.

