### Randomization

Randomization will be performed after the eligibility assessment and baseline assessment. The Department of Science and Technology of SUTCM will generate the randomization sequence using a random number generator (IBM, Chicago, IL, USA) and then placed in a sequenced, sealed, opaque envelope. When potential participants meet the inclusion criteria, the envelope can be opened and the subject will accept the corresponding measures. Then, eligible patients will be randomly divided into a guideline therapy group and a guideline therapy plus TCMR group, with an allocation proportion of 1:1.

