#### Analysis of primary outcome

The primary outcomes will be evaluated at baseline, 6 days after the intervention, and upon discharge based on the intention-to-treat analysis (ITT). The primary endpoint of the trial is the mean change in mMRC Scales from baseline to the discharge day. Baseline covariates included for adjustment were sex, age category, history of cardiopulmonary disease, and body weight category. The whole outcomes scale was also measured at baseline. When the data have a normal distribution, two-way repeated-measures ANOVA will be used as the main analytic method, and a paired sample *t* test will be used between the two intervention groups; if the normal distribution is not met, the Wilcoxon test will be used as an alternative method. Prior to any analysis, any missing data pattern will be investigated and reasons for missing data obtained and summarized where possible. The percentage of missing data is 20%, and we plan to generate 5 imputed datasets, which is the minimum recommended number [28]. The sensitivity analyses were carried out to assess two assumptions about missing data, and data imputation scenarios can potentially influence the primary result [29]. To account for missing data, our primary analyses were conducted on an imputed data set where missing values were generated using multiple imputation by chained equations (MICE) [30].

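### Exclusion criterion (6) would remove randomised patients for exercise taken after allocation, which conflicts with intention-to-treat and overlaps with the exercise allowed in both groups

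*Protocol article*

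**What the plan says.** All of this is in the protocol article.

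- **Inclusion criteria, item (5):** patients must "promise not to perform other exercise programs".
- **Exclusion criteria, opening line:** "Those who meet one of the following conditions will be removed". The last condition, numbered (6), is "patients who participate in other forms of exercise during the trial".
- **Interventions, last sentence:** participants in both groups are "allowed to participate in normal exercise under the intervention conditions".
- **Randomization:** "Randomization will be performed after the eligibility assessment and baseline assessment".
- **Blinding:** participants and therapists cannot be blinded; outcome assessors, data managers and statisticians are.
- **Analysis of primary outcome:** the primary outcome is evaluated "based on the intention-to-treat analysis (ITT"), with multiple imputation for missing values. The endpoint is the mean change in mMRC from baseline to discharge.

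The article does not define or distinguish the three exercise terms. It does not say whether a patient removed under (6) is still followed and analysed.

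**The concern.** An exclusion criterion should be decidable before allocation. Criterion (6) describes what a patient does while on trial, so it acts mainly as a removal rule after randomisation.

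That matters for three reasons. First, the arms differ in what they are offered: only the test group has a training programme, with nurse reminders, diary sign-in and rewards for completing it (Adherence). Both the taking of other exercise and its detection could therefore differ by arm. Second, patients and therapists know the allocation. Third, being able to exercise is plausibly related to breathlessness, which mMRC grades. Removal linked to both arm and outcome undoes the protection that randomisation gives, and intention-to-treat exists to prevent that.

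The overlap in terms makes it worse. If staff cannot tell permitted exercise from exercise that leads to removal, the decision rests on unblinded local judgement.

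**Working it through.** **1. When can each statement be applied?**

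- Inclusion (5) is a promise and can be checked at screening.
- Exclusion (6) is conduct on trial. It can be checked at screening only as an intention, and then it merely repeats inclusion (5). To add anything, it must act later.
- Randomisation follows eligibility and baseline assessment, and treatment follows randomisation. Acting later therefore means, for the most part, acting on allocated patients.

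**2. Do the exercise statements agree?**

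- Inclusion (5) against Interventions: compatible if the first means structured programmes and the second means ordinary activity.
- Exclusion (6) against Interventions: (6) speaks of forms of exercise, not programmes. That is wide enough to include ordinary exercise, so the two overlap unless a line is drawn. None is.

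**3. Does removal fit the analysis set?** Intention-to-treat keeps each randomised patient in the assigned arm. If removal ends follow-up, the discharge mMRC is lost and at best imputed. If removal means leaving the data set, the analysis is not intention-to-treat. The article does not rule out either.

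**4. Can the bias be sized?** For each arm let p be the share removed and g the mean change in mMRC of removed patients minus that of retained patients. Removal shifts an arm mean by −p × g, so the bias in the difference (TCMR minus control) is

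p(control) × g(control) − p(TCMR) × g(TCMR).

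The documents give none of these four quantities. The bias is zero if the products are equal and can take either sign otherwise.

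**5. What would removal cost in power?** Inputs from Sample size calculation: means 0.52 and 0.95, SDs 0.11 and 0.92, α 0.05 (two-sided under General analysis principles), β 0.10, 20% loss, 64 per group.

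- Difference: 0.95 − 0.52 = 0.43. Root-mean-square SD: √((0.11² + 0.92²)/2) = 0.655.
- The plan's figure reproduces: the unequal-variance t-test needs 51 per group, and 51/0.80 = 63.75, rounded up to 64.
- Power by normal approximation is Φ(0.43/(0.655 × √(2/n)) − 1.96). After 20% loss, n = 64 × 0.80 = 51.2.

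| Removed on top of 20% loss (assumed) | n per group | Power |
|---|---|---|
| 0% | 51.2 | 91% |
| 5% | 48.6 | 90% |
| 10% | 46.1 | 88% |
| 20% | 41.0 | 84% |

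The loss of power is modest. The issue is selection, and the planned sample size is not affected.

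**The case against.** The best defence is that the removal line heads the whole exclusion list. Most items there, such as pregnancy and serious mental illness, are screening conditions, so being removed may simply mean not being enrolled. Exits after enrolment have their own section, Dropout and suspension criteria, which names withdrawal and a short stay but not exercise. Normal exercise may also mean everyday activity, and the permission is qualified by reference to the intervention conditions.

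Part of this stands. The exercise contradiction is one of overlapping, undefined terms, not a flat ban set against a flat permission. That randomised patients leave the analysis is what (6) implies if applied as written; it is not stated outright. But a criterion about conduct on trial cannot be settled at screening, however the exercise terms are defined. Nor is removal after enrolment foreign to this protocol: "if the hospitalization time is less than 7 days, the subject will be excluded as the outcome evaluation cannot be completed". That rule is a separate matter and adds no weight here.

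A reader might go further and infer that controls, who get no training, exercise more on their own, that exercisers are less breathless, and that removing them favours TCMR. With assumed shares of 15% (control) and 5% (TCMR) and a gap of 0.5 to 1.0 grade, this gives (0.15 − 0.05) × 0.5 = 0.05 to (0.15 − 0.05) × 1.0 = 0.10 grade. The documents do not support it:

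- No section says controls exercise more. Guideline therapy asks for adequate rest, and wards are remotely monitored. Closer observation of TCMR training could equally detect more exercise in that arm.
- The calculation shifts mMRC levels, but the endpoint is change. A patient lower by the same amount at baseline and at discharge has the same change as others. One who starts near 0 has less room to improve, and removing such patients could work against TCMR.
- The assumptions do not fit the planning values if 0.52 is a score, as the article calls it. With 15% of controls 1.0 grade lower, the others average 0.52 + 0.15 = 0.67 and the exercisers 0.67 − 1.0 = −0.33, which is impossible on a 0–4 scale. At 0.5 grade lower, the mixture alone gives an SD of 0.5 × √(0.15 × 0.85) = 0.18, above the stated 0.11.

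**Conclusion.** The point holds as a defect in the rule. Criterion (6), applied as worded, removes randomised patients for unblinded conduct after allocation and conflicts with the stated intention-to-treat analysis. This does not depend on how the exercise terms are read. The overlap between (6) and the exercise permitted in both groups is a weaker, secondary point, because a reading exists under which the terms differ.

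The conclusion assumes that (6) is meant to operate while patients are on trial, as its words say. No direction or size of bias is claimed: the rates of other exercise, and the outcomes of those who take it, are not in the documents. The correction should be made because it is cheap and protects the randomised comparison.

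**What to change.** 1. Reconcile inclusion (5), exclusion (6) and the last sentence of Interventions into one exercise statement with defined terms. Its content is a clinical matter for the sponsor.
2. Limit exclusion (6) to what is known before randomisation.
3. State in Analysis of primary outcome that patients who take other exercise after randomisation are still followed to discharge and analysed in their assigned arm.
4. Record other exercise in the same way in both arms, and use it only descriptively or in a sensitivity analysis.
5. If any patients have already been removed under (6), report their number by arm and include whatever outcome data exist for them.

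The cost is a wording change and, if the case report form (not shown) does not already capture other exercise, one added item. No extra patients are needed.

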### Guideline therapy

The health authorities have drafted a conventional treatment plan for patients with severe conditions; this is described below. (1) Patients should ensure adequate rest time, and medical staff need to closely monitor vital signs, oxygen saturation, etc. (2) Additionally, it is necessary to monitor routine blood and urine tests, C-reactive protein, biochemical indicators, blood coagulation function, arterial blood gas analysis, chest imaging, etc. according to the changes in the condition. (3) Timely effective oxygen therapy measures should be taken; in particular, patients with severe disease should receive a nasal cannula or mask to inhale oxygen, and whether respiratory distress and/or hypoxemia is relieved should be promptly evaluated. (4) Doctors should use antiviral drugs combined with antibiotics if necessary. (5) To maintain the stability of the internal environment, they should strengthen supportive treatment to ensure sufficient heat and pay attention to water and electrolyte balance. (6) In addition, early Chinese medicine can be used to relieve syndromes.

### Guideline therapy plus TCMR

Conventional treatment as the authorities have required will be the same as that of the control group. In addition, acupressure therapy and Liu Zi Jue Qigong exercises will be carried out in the TCMR program.

#### Acupressure therapy

The specific acupressure process will be as follows. According to channel-collateral theory, severe cases display a lung qi deficiency pattern characterized by a weak cough, dyspnea, low voice, and clear watery sputum with other symptoms of qi deficiency. Therefore, acupoints related to the lung viscera including Feishu (T 3), Danzhong (CV 17), and Zhongfu (Lu 1) will be selected [17]. Pressing these points can improve lung symptoms [3]. First, the patient will take a sitting or lying position with the therapist on the patient’s right side. Pressing and kneading constitute the manipulation of acupressure. The first step is called the continuous shiatsu method. The therapist uses the thumb pad to press on the selected acupuncture points with moderate force, which is approximately 10 N as tested by a mechanical instrument [18]. The direction of the pressure should be perpendicular to the skin surface, and the pressure is held for 3–7 s and then relaxed without leaving the skin surface. The second step is kneading the acupoint with the thumb. The thumb acts on the skin surface of the acupoint with a slight force pressure (5 N) and then performs a small circular sliding movement with the acupoint at the center. This procedure is performed 50 times on each acupoint with the pressing method and kneading method. The acupressure operation is shown in Fig. 3.

**Fig. 3 Fig3:**
[figure not shown]
Acupressure operation

#### Liu Zi Jue Qigong exercises

Liu Zi Jue Qigong exercises are performed as follows: (1) Preparation phase—the patient is standing with the body in a relaxed state, and abdominal breathing or nasal suction is used to relax the abdominal muscles. The diaphragm is contracted together without breathing for 3 s. (2) Practice phase—whistling with the lips is performed to make the “xu, he, hu, si, chui, and xi” sounds lasting for 5 s each. After each of the 6 pronunciations, the patient returns to the ready posture and then performs the next exercise. Each voice exercise is repeated 12 times. The basic seven movements of the exercise are shown in Fig. 4.

**Fig. 4 Fig4:**

The basic seven movements of the exercise

### Adherence

Acupressure therapy will be conducted by the physiotherapists every day, and they will complete a recording daily. The nurse will inform the patient to perform Liu Zi Jue exercises every day at 9 am and 4 pm. Each ward has remote monitoring so that remote monitoring of the training of the subject can be achieved, and the participants will be required to sign in a diary after each exercise. Eventually, participants who can complete the training will be rewarded with monetary rewards.

### Plan for retaining participants

An adequate retention plan is a valuable component of the research design process that can enhance participants’ ties with the researchers and the study [19]. First, we will establish a local retention working group including the research coordinator and nurses. The coordinator and nurse will be fully trained before the trial starts; by focusing on daily communication strategies, they can improve retention after receiving additional attention [20]. Furthermore, it is useful to provide sufficient funds within the study budget to compensate the nurses and participants for retention. Subjects will be monitored from a distance while completing their daily physical therapy with a diary recording.

### Outcome measurements

All outcomes will be managed by researchers masked to the group assignment; the outcomes will include the Modified Medical Research Council Dyspnea Scale, Activities of Daily Living Barthel Index Scale, Patient Health Questionnaire-9 Scale [21], and Respiratory Symptoms Scale. Evaluation of the outcomes will occur at three points (before treatment, the 7th day during hospitalization, and the discharge day).

### Primary outcome measurements

#### Modified Medical Research Council (mMRC) Dyspnea Scale

We will use the mMRC as the primary outcome indicator to evaluate the dyspnea symptoms and physical health; this scale is a good indicator of the functional capacity of patients’ lungs [22]. Evaluation of the outcomes will occur at three points (before treatment, the 7th day during hospitalization, and the discharge day). The mMRC [22, 23] grades are as follows: mMRC grade 0, dyspnea occurs only during strenuous exercise; mMRC grade 1—the patient has shortness of breath when walking on flat ground or walking on a small slope; mMRC grade 2—due to shortness of breath, when walking on flat ground, the patient is slower than another person of the same age or needs to stop to rest; mMRC grade 3—when walking on flat ground for approximately 100 m or after a few minutes, the patient needs to stop to pant; and mMRC grade 4—due to severe breathing difficulties, the patient cannot leave the house or has breathing difficulties when dressing or undressing. We will assess the mMRC with a repeated longitudinal analysis.

### Secondary outcome measurements

#### Activities of Daily Living Barthel Index (ADL-BI) Scale

The Barthel Index (BI) is one of the most commonly used methods to assess a person’s basic self-care ability and the intensity of care required; this measure is better suited to acute settings [24–26]. If the total score is greater than 40, the patient is considered more capable. The BI mainly includes 10 daily life behaviors, such as eating, bathing, dressing, and controlling bowel movements. Each item can be scored 10 points if it can be completed independently. Five points are needed for partial help. A total score of 100 indicates that the patient can perform daily activities and does not need to depend on others. A score of > 60 is considered good, indicating that the patient has mild dysfunction and is able to take care of his- or herself in basic daily life. A score of 60–41 indicates moderate dysfunction, and it is obvious that in daily life, the patient depends on others. A score < 20 indicates that the patient is completely disabled, and his or her daily life is completely dependent on others. A repeated longitudinal analysis will also be used to evaluate the ADL-BI.

#### Patient Health Questionnaire-9 (PHQ-9) Scale

The PHQ-9 is used to detect and measure depression and severity in medical populations in clinical settings; this scale has been implemented in a variety of settings using medical populations. It is a questionnaire evaluating the frequency of 9 negative items that happened to patients in the last 2 weeks. If the answer is not at all, the score is 0 points; if once every few days, the score is 1 point; if once more than half a day, the score is 2 points; and if every day, the score is 3 points. The PHQ-9 score is divided into the following categories of increasing severity: 0–4, 5–9, 10–14, 15–19, and 20 or greater. The PHQ-9 results will be assessed using a repeated longitudinal analysis.

#### Respiratory Symptoms (RS) Scale

Respiratory symptoms include fatigue, cough, expectoration, chest tightness, dyspnea, sore throat, nasal congestion, runny nose, and some other nonspecific symptoms. The severity of these symptoms is recorded sequentially as 0–10, with 0 being no and 10 being the most severe. These are self-evaluation scales that will be evaluated with a repeated longitudinal analysis.

### Sample size calculation

The PASS software (PASS 11, NCSS, LLC, Kaysville, UT, USA) will be used to estimate the sample size utilizing two independent sample means (*α* = 0.05, *β* = 0.10). We will use the mMRC as the primary efficacy outcome. Based on previous clinical studies on the effect of respiratory symptoms after acupressure therapy plus Liu Zi Jue Qigong interventions, the mMRC Scale score in the control group is 0.52 with a standard deviation of 0.11 [27], and the average mMRC Scale score in the treatment group is 0.95 with a standard deviation of 0.92. In this study, the target sample size will be 64 participants in each group, anticipating on maximum loss to follow-up of 20%.

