### Statistical analysis

#### General analysis principles

Statistical analysis will be performed using IBM SPSS version 25.0 (IBM Corp., Armonk, NY, USA). A Kolmogorov-Smirnov test with Lilliefors correction will be used to analyze all quantitative variables to determine whether they follow a normal distribution. Nonnormally distributed data will be expressed as the median (upper and lower quartiles), and normally distributed data will be expressed as the mean ± the standard deviation (SD). Categorical variables will be presented as frequencies and percentages. The level of significance will be *α* < 0.05 with a two-tailed test, and 95% confidence intervals will be presented where appropriate.

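### The control-arm SD of 0.11 behind 64 per arm is impossible on a whole-grade scale, so the 90% power claim is unsupported; separately, the planning means are mislabelled or reversed

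*Protocol article*

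**What the plan says.** The protocol article, under Sample size calculation, compares two means "utilizing two independent sample means (*α* = 0.05, *β* = 0.10"), that is, with 90% power. General analysis principles fixes the sidedness: "with a two-tailed test". For the control arm the planning input is that "the mMRC Scale score in the control group is 0.52 with a standard deviation of 0.11"; for the intervention arm, "the average mMRC Scale score in the treatment group is 0.95 with a standard deviation of 0.92". From these, "the target sample size will be 64 participants in each group", "anticipating on maximum loss to follow-up of 20" per cent.

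The section on the mMRC scale defines five whole grades from 0 to 4, with breathlessness increasing by grade. At grade 4, "due to severe breathing difficulties, the patient cannot leave the house" or struggles to dress. Under Analysis of primary outcome, "The primary endpoint of the trial is the mean change in mMRC Scales from baseline to the discharge day". Background and Study design set out a superiority trial in which adding TCMR is expected to do better than guideline therapy alone.

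**The concern.** Two separate things look wrong in the planning inputs.

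The first is the control SD. An SD of 0.11 around a mean of 0.52 would need almost every patient to sit close to 0.52, but a patient can only be at 0, 1, 2, 3 or 4. If this value drives the sample size, the claimed type II error of 10% has no basis, and a null result could be read as coming from a trial with 90% power when it did not.

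The second is the label and direction of the means. Both are called scores. On this scale a higher score is worse, so 0.95 on TCMR against 0.52 on control describes the opposite of the hypothesis. The primary endpoint is a change from baseline, and the section does not say whether 0.52 and 0.95 are changes. A reader cannot tell which quantity was powered.

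**Working it through.** **Inputs.** From Sample size calculation: means 0.52 and 0.95 (difference 0.95 − 0.52 = 0.43), SDs 0.11 and 0.92, α = 0.05, power 0.90, 64 per arm, loss up to 20%. From General analysis principles: two-sided test. From Randomization: 1:1 allocation. Evaluable per arm at full loss: 64 × 0.8 = 51.2, taken as 51.

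**1. Reproduce the stated size.** Normal approximation: n = (1.960 + 1.282)² × (0.11² + 0.92²) / 0.43² = 48.8, so 49 per arm. The unequal-variance (Welch) t test raises this to 51 (power 89.6% at 50, 90.2% at 51). Allowing for loss, 51 / 0.8 = 63.75, so 64. This matches the document exactly, so the arithmetic is sound and 0.11 was used as an SD.

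**2. Smallest possible SD.** For a whole-number variable with a given mean, the SD is smallest when all values lie on the two neighbouring integers. For mean 0.52 these are 0 and 1, which gives sqrt(0.52 × 0.48) = 0.4996, or 0.50. A difference between two whole grades is also a whole number, so the bound is the same for a mean change of 0.52 in either direction. The stated 0.11 is less than a quarter of this minimum. The treated SD passes the same check: sqrt(0.95 × 0.05) = 0.22, below 0.92.

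**3. Power with a possible control SD.** Two-sided Welch t test, difference 0.43 and treated SD 0.92 held as stated:

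| Control SD | Power, 51 per arm (20% loss) | Power, 64 per arm (no loss) | Evaluable per arm for 90% | Randomised per arm (÷ 0.8) |
|---|---|---|---|---|
| 0.11 (stated) | 90.2% | 95.5% | 51 | 64 |
| 0.50 (minimum) | 82.5% | 90.2% | 64 | 80 |
| 0.70 (assumed) | 74.8% | 83.9% | 77 | 97 |
| 0.92 (assumed equal SDs) | 64.7% | 74.7% | 98 | 123 |

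**4. Difference detectable with 90% power at 51 per arm.** About 0.48 grade at control SD 0.50 and about 0.60 at 0.92, against the planned 0.43.

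**5. Direction.** Changing the sign of the 0.43 difference leaves a two-sided sample size and power unchanged. All of the loss in step 3 therefore comes from the SD. The direction is a fault of labelling or of content, with no numerical consequence for N.

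**The case against.** The strongest objection is that the true power is unknown. The figures above hold the difference at 0.43 and the treated SD at 0.92, and both come from the same two lines as the impossible SD. If the treated SD were also smaller, 90% could be reached: a common SD of 0.66 gives 90.3% at 51 per arm, and SDs of 0.50 (control) and 0.75 (treated) give 92.1%. In the other direction, a control SD of 1.10 with treated SD 0.92 gives 56%. The document also describes 20% as a maximum loss. At the minimum control SD, 10% loss (58 per arm) gives 87%, and no loss gives 90.2%. All of this stands. A reader might infer that the trial is shown to have less than 90% power. The document does not support that; it shows only that the 90% claim rests on an impossible number.

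A reader might also infer that the reversed means contribute to the shortfall, or that the trial was designed to show harm. Neither follows. The sign does not enter a two-sided calculation, and if 0.52 and 0.95 are improvements in grades, the direction is right, they fit the change endpoint, and only the word for them is wrong. The SD of 0.11 would remain impossible on that reading.

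It could be said that multiple imputation or baseline adjustment would recover power. The sample size section claims no such gain, and imputation does not restore the full information of lost patients. Nor is this a detail left out of a condensed article: the value is stated, and it is wrong.

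**Conclusion.** The point holds in two parts.

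First, a control SD of 0.11 is mathematically impossible for whole grades, or whole-grade changes, with mean 0.52. The stated 64 per arm depends on it. This conclusion needs only the scale definition and the stated mean. With difference 0.43, treated SD 0.92 and the full 20% loss, power is at most about 83%, so the type II error is at least about 17% instead of the stated 10%. It is about 35% if both SDs are 0.92, which is an assumption. The range of 65% to 83% is illustrative and conditional on those inputs; it is not a bound on the true power.

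Second, and independently of power, the means as labelled contradict the superiority hypothesis and are not tied to the change-from-baseline endpoint.

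The fault lies in the inputs, not in the calculation made from them. How 0.11 arose cannot be settled from the document. A standard error entered as an SD is one possibility, since (0.92 / 0.11)² is about 70 patients, but that is conjecture.

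**What to change.** Keep N = 128: recruitment was expected to end on 30 June 2020 and this protocol version is dated 8 July 2020. In the sample size section:

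- Check all four planning values against the cited source.
- State whether 0.52 and 0.95 are improvements or post-treatment grades, and correct the label and direction so that they agree with the hypothesis and the change endpoint.
- Replace 0.11 with a feasible per-patient SD of the mMRC change. It must be at least 0.50 if the mean is 0.52; for another mean with fractional part f, at least sqrt(f(1 − f)).
- Recompute, from the corrected inputs, the power or the difference detectable with 90% power, for 64 per arm with up to 20% loss.

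Until the source is checked, 65% to 83% power, or a detectable difference of 0.48 to 0.60 grade, may be given only as an illustration, with its conditions stated: treated SD 0.92, control SD from 0.50 to 0.92, 51 evaluable per arm and, for the power figures, difference 0.43.

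The cost is a rewording of one section and, in all likelihood, a less favourable power statement. No extra patients and no change to the analysis are needed.
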